**Methods:**

This is a randomised, participant- and assessor-blinded, cross-over clinical trial. Thirty healthy volunteers (male:female ratio 1:1) will be randomised to general anaesthesia by either sevoflurane or propofol. Multimodal magnetic resonance imaging (MRI) of the brain will be performed before and after general anaesthesia and repeated after 1 and 8 days. Each magnetic resonance imaging session will be accompanied by cognitive testing and questionnaires on fatigue and well-being. After a wash-out period of 4 weeks, the volunteers will receive the other type of anaesthetic (sevoflurane or propofol), followed by the same series of tests. Primary outcomes: changes in T1-weighted 3D anatomy and diffusion tensor imaging. Secondary outcomes: changes in resting-state functional magnetic resonance imaging, fatigue, well-being, cognitive function, correlations between magnetic resonance imaging findings and the clinical outcomes (questionnaires and cognitive function). Exploratory outcomes: changes in cerebral perfusion and oxygen metabolism, lactate, and response to visual stimuli.

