**Total score ≥ 4 predicts difficult intubation**			

### Outcomes

Outcome parameters will be measured before and after GA, and subsequently after 1 and 8 days. Possible differences can, thus, be assessed before and after GA, within each type of general anaesthesia, and between GA methods (sevoflurane vs. propofol).

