#### Secondary outcomes

Differences in resting-state functional MRI (rsfMRI)Severity and characteristics of fatigue, as measured by Multidimensional Fatigue Inventory (MFI-20) [42]Cognitive function including attention, speed, and executive functions as measured by computer-based neuropsychological tests (Paced Auditory Serial Addition Test (PASAT), Test of Attentional Performance (TAP) and Conners Continuous Performance Test, 3rd edition (CPT3))Quality of Recovery – 15-item questionnaire (QoR) [43]Correlations between MRI findings as well as clinical outcomes as described above

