### Cognitive performance tests

The Test of Attentional Performance (TAP) in this study consists of Crossmodal Integration, Go/Nogo, Incompatibility and Flexibility. They measure cognitive integration, attention and flexibility in response to auditive and visual stimuli (TAP 2.3.1 12/2016 from Psytest, D-52134 Herzogenrath). The Paced Auditory Serial Addition Test (PASAT) measures auditive working memory [52]. Conners Continuous Performance Test, 3rd edition (CPT3) measures persistent attention (CPT3, MHS 2014).

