### Quality of Recovery-15 Questionnaire and Multidimensional Fatigue Inventory

The volunteers fill in the validated Quality of Recovery Questionnaire (QoR-15) [43] and the Multidimensional Fatigue Inventory (MFI-20) [42]. The QoR-15 questionnaire results in a score of 0–150. The MFI-20 covers aspects of general fatigue, physical fatigue, mental fatigue, motivation and activity in 20 statements with five-scale ratings of agreement.

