### Statistical analysis

The distribution of continuous data is rated for normality using residual-plot or by the Shapiro-Wilk W test. Normality can be reached by simple transformation (log, logit). Statistical comparison of paired data is performed with parametric or non-parametric method or by analysis of variance (ANOVA). Depending on the distribution, testing is performed with Mann-Whitney or Wilcoxon tests, respectively. The risk for Type I errors is reduced by reducing the significance level to 0.05 (alpha). A general summation goal will be used to avoid mass-significance by repeated measurements. In statistical measurements where multiple comparisons cannot be avoided, Duncan’s corrections (i.e. secondary outcome parameters) are performed. For MRI data, correction for multiple comparisons is performed with Bonferroni’s correction or the false discovery rate (FDR). For statistical comparison between categorical variables (i.e. psychometric data) the *X*^2^ test with Yates’ correction is performed.

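### Duncan's procedure, named as the correction for secondary outcomes, does not hold the error at 5% within a score once more than two time points are compared

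*Protocol article*

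**What the plan says.** The Statistical analysis section of the protocol article deals with multiplicity in several sentences:

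- On the significance level: "The risk for Type I errors is reduced by reducing the significance level to 0.05 (alpha").
- Next comes an undefined summation approach, meant to prevent spurious significance from repeated measurements.
- For what remains: "where multiple comparisons cannot be avoided, Duncan’s corrections (i.e. secondary outcome parameters) are performed".
- Bonferroni or the false discovery rate is given for MRI data only.

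The section on correction for multiple comparisons adds a level of 0.025, for the two primary endpoints only.

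The secondary outcomes include MFI-20, QoR-15, PASAT, TAP and CPT3. Under Outcomes: "Outcome parameters will be measured before and after GA, and subsequently after 1 and 8 days". The abstract confirms that this covers the clinical scores: "Each magnetic resonance imaging session will be accompanied by cognitive testing and questionnaires on fatigue and well-being". Each score therefore has four means per session. TAP "consists of Crossmodal Integration, Go/Nogo, Incompatibility and Flexibility", and "The MFI-20 covers aspects of general fatigue, physical fatigue, mental fatigue, motivation and activity in 20 statements".

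For comparing data, the Statistical analysis section lists parametric and non-parametric methods, ANOVA, and the Mann-Whitney and Wilcoxon tests. It does not make Duncan's test conditional on a significant ANOVA.

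**The concern.** A multiplicity correction is there to keep the chance of any false difference near a stated level. Duncan's test does not do this by design. It allows a fresh 5% for each additional mean in the range, so its familywise error grows with the number of time points.

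It is also a range test among the means of one variable. It offers nothing across different scores, although the bracketed reference to secondary outcome parameters could be read as intending that. It has no standard form for the Wilcoxon or Mann-Whitney tests that the same section allows.

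At stake is how far a significant change over time in a fatigue, recovery or cognitive score can be trusted. A reader told that the comparisons were corrected would take the protection to be stronger than it is.

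**Working it through.** **The plan's own figure.** The protocol gives no error rate for Duncan's test. The figures it does give are alpha 0.05 and, for the two primary endpoints, 0.05/2 = 0.025, which is reproduced exactly. Neither says what Duncan's test delivers for the secondary outcomes.

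**Inputs.** Alpha 0.05 (Statistical analysis); four time points per session (Outcomes); two anaesthetics per volunteer and 30 completers (Study design).

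**Step 1: error by formula.** For p means Duncan's protection level is (1 − alpha)^(p−1). With no true differences, the familywise error is 1 − 0.95^(p−1):

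| Means compared | Calculation | Error |
|---|---|---|
| 2 | 1 − 0.95 | 5.0% |
| 3 | 1 − 0.95² | 9.75% |
| 4 (one session) | 1 − 0.95³ | 14.3% |
| 8 (both sessions) | 1 − 0.95⁷ | 30.2% |

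**Step 2: why it happens.** With 30 volunteers and four repeated means, the within-volunteer error has (30 − 1) × (4 − 1) = 87 degrees of freedom. For the range of all four means, Duncan uses the 0.95³ = 0.857 quantile of the studentised range, which is 3.06. Tukey uses the 0.95 quantile, 3.70. Duncan's lower bar produces the excess.

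**Step 3: simulation.** 20,000 runs, n = 30, four repeated means, within-volunteer error term. Entries are the chance of any false difference in one score.

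| Situation | Duncan, no gate | Duncan after significant F | Tukey |
|---|---|---|---|
| No effect, equal correlations (0.6) | 14.3% | 5.1% | 5.2% |
| No effect, serial correlation | 15.1% | 6.8% | 6.6% |
| One time point shifted, equal correlations | 9.5% | 9.5% | 2.8% |
| One time point shifted, serial correlation | 13.3% | 13.3% | 5.0% |

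A separate simulation of the no-effect case gave 14.1% for ungated Duncan, 5.0% for Tukey and 4.5% for Holm on the contrasts with baseline.

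The third row shows the limit of an F gate. One real change opens the gate, and the three unchanged means are then compared at 1 − 0.95² = 9.75%. The simulated 9.5% agrees with this.

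**Step 4: when the problem vanishes.** If the summation approach reduces a score to one value per anaesthetic, there are two means, and Duncan's error is 5.0%.

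**The case against.** **The 14.3% depends on how Duncan is run.** ANOVA is named in the same section, and as a follow-up to a significant F test Duncan's error is about 5% when nothing changes. This stands as a limit on the figure. No gate is stated, however, and a gate does not help once one time point truly differs (about 9.5%).

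**The summation sentence may remove the repeated time points.** This also stands. It could leave two means for some scores. But the approach is undefined, and Duncan is named precisely for the comparisons that remain.

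**The protocol does not claim a familywise 5% for Duncan.** That is correct: alpha 0.05 is in a separate sentence. Still, a procedure named as a correction, in a passage about limiting Type I error, should control that error.

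**Stronger readings that the documents do not support.** A reader might infer that the third hypothesis (reduced well-being and executive function, more so after sevoflurane) would be confirmed by chance in most null trials. It would not. The hypothesis is directional and refers to baseline, whereas the 14.3% counts any pair of time points in either direction. Counting only false deteriorations from baseline, ungated Duncan gives 4.6% per score, and gated Duncan 2.0%.

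A reader might also multiply the error over a dozen scores. That needs a count of scores and correlations that the protocol does not give. The Secondary outcomes section names fatigue only "as measured by Multidimensional Fatigue Inventory (MFI-20"), so testing its five aspects separately is an assumption.

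Nor is the lack of a correction across all secondary scores an error. Such control is not obligatory and is commonly left to the analysis plan, which is not shown.

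**Conclusion.** The point holds in a narrow form. The correction that the protocol names does not hold familywise error at 5% within a score when more than two means are compared.

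For the four time points of one session the rate is 14.3% if Duncan is run without a gate. With an unstated F gate it is about 5% under no effect and about 9.5% if one time point truly differs; serial correlation raises these to 6.8% and 13.3%. For a score reduced to two means there is no excess.

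These figures assume all pairwise comparisons, roughly normal data and the within-volunteer error term. Where rank tests are used instead, the named correction has no standard form. It cannot act across scores in any case.

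Severity is minor. The primary outcomes have their own stated correction and are unaffected.

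**What to change.** Delete the reference to Duncan. For fatigue, recovery and cognition, prespecify the within-volunteer contrasts: each follow-up against its own baseline, and sevoflurane against propofol. Adjust them by Holm at 5% within each score, or within each of the three domains, and state that control is at that level. Holm works on p-values, so it also serves where a Wilcoxon test replaces a parametric one. If summation is to reduce the time points for a score, define the summary and say which scores it applies to.

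The change is one of wording. Its cost is fewer nominally significant secondary findings. As an illustration, suppose each score has nine contrasts: three follow-ups against baseline for each of two anaesthetics (6), plus three between anaesthetics. Holm's first threshold within a score is then 0.05/9 = 0.0056. With 30 pairs, 80% power at that threshold needs a standardised paired difference of about 0.71, against 0.53 at an unadjusted 0.05 (paired t test, noncentral t).

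Per-domain control is stricter. With six cognitive scores (PASAT, four TAP subtests, CPT3; an assumed count) the first threshold is 0.05/(6 × 9) = 0.0009, and the corresponding difference is about 0.84. Fewer prespecified contrasts would lower this cost. Adjustment over all scores and contrasts together is not asked for.

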### Missing data

For all analyses, an intention-to-test (ITT) analysis will be performed including all subjects that participated in at least one study session. Analyses will be based on all observed data. If missingness exceeds 5% and there is indication of violation of ‘missing completely at random’ (MCAR) by a statistically significant Little’s test, a sensitivity analysis based on an appropriate model for missingness at random (MAR) or not at random (MNAR) will be performed.

### Sample size

We base our sample size estimations on the following primary end points: (1) changes in grey-matter volume, and (2) DTI changes. The volunteers will serve as their own controls.
(i)*Sample size estimation based on changes in grey-matter volume*: we base our sample size estimation for grey-matter volume changes on data extrapolated from the hippocampus. The mean volume of the hippocampus is approximately 2.50 mL (± 0.15 standard deviation (SD)) in the healthy population [54]. The pre-operative hippocampal volume has been found to be 6% smaller in patients suffering from POCD compared to patients not suffering from POCD [55]. We assume that GA will affect the grey-matter volume to a larger extent compared to e.g. vulnerability towards POCD. Thus, 25 subjects will be necessary to detect a difference of 8% in the hippocampal volume between groups, applying a two-tailed alpha value of 0.05, SD ± 10% and a desired power of 0.80(ii)*Sample size estimation based on DTI changes*: our sample size estimation for detection of DTI changes is also based on data extrapolated from the hippocampus. We assume a 10% change in mean diffusivity, since we expect GA to induce larger changes than, e.g. a learning task by video gaming [56]. With a significance level of 0.05, a power of 80%, a SD of ± 10%, this indicated a required sample size of 16 volunteers

#### Correction for multiple comparisons

Since it should be assumed that grey-matter changes and changes in DTI are inter-dependable variables, the significance level for each sample size estimation should be corrected for multiple comparisons. The desired corrected significance level is 0.025 (significance level of 0.05 Bonferroni corrected for two number of hypothesis). With a SD of ± 10% and 80% power, this gives a sample size of 30 volunteers regarding detection of statistically significant differences in grey-matter volume. Regarding statistically significant differences in DTI, the calculation gives a sample size of 20 volunteers. We are therefore confident that a sample size of 30 volunteers will be sufficient to ensure the necessary statistical power.

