#### Primary outcome

Volume and morphology of the brain’s anatomical structures as recorded by T1-weighted three-dimensional (T1w3D) anatomical MRI scans, and white-matter microstructure as measured using diffusion tensor imaging (DTI)

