### Detection of differences between general anaesthesia methods

For detection of differences between GA methods, we estimate a 10% difference between the two GA methods with regard to both grey-matter changes and changes in DTI. With a significance level of 0.025 (Bonferroni corrected), SD ± 10% and a power of 80%, the sample size is 20. We therefore choose to include 30 volunteers to ensure sufficient power.

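### Alpha is corrected for two hypotheses, but the sizing sections apply the same 0.025 to at least four primary comparisons, and no primary scan or contrast is named

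*Protocol article*

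**What the plan says.** **Endpoints.** The Primary outcome section defines the outcome by imaging modality. It lists "Volume and morphology of the brain’s anatomical structures as recorded by T1-weighted three-dimensional (T1w3D) anatomical MRI scans" and, alongside this, white-matter microstructure by DTI. It names no scan and no contrast.

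**Scans and contrasts.** The Outcomes section states: "Outcome parameters will be measured before and after GA, and subsequently after 1 and 8 days". Each session therefore has one baseline and three post-anaesthesia scans. The section continues: "Possible differences can, thus, be assessed before and after GA, within each type of general anaesthesia, and between GA methods (sevoflurane vs. propofol". The Hypotheses section likewise contains both a change from baseline under either agent and a larger change under sevoflurane than under propofol.

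**Level.** The Sample size section begins: "We base our sample size estimations on the following primary end points: (1) changes in grey-matter volume, and (2) DTI changes". The next section then sets the level: "The desired corrected significance level is 0.025 (significance level of 0.05 Bonferroni corrected for two number of hypothesis". The section on differences between anaesthesia methods applies that level again, for both endpoints: "With a significance level of 0.025 (Bonferroni corrected), SD ± 10% and a power of 80%, the sample size is 20".

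**Analysis provisions.** Statistical analysis gives a level of 0.05 and adds: "A general summation goal will be used to avoid mass-significance by repeated measurements". It also provides for Bonferroni or FDR correction of MRI data.

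**The concern.** Dividing 0.05 by two is right for a family of two tests. Here each of the two endpoints is sized for more than one primary question, and every question uses the level that was split only between the endpoints. The family that 0.025 protects is therefore smaller than the set of comparisons presented as primary.

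The missing choice also affects interpretation. MRI 2 takes place on the day of anaesthesia, after at least 2 hours of observation, and MRI 4 takes place 7–10 days later. A same-day change and a change still present at a week are different findings. So are a change after one agent and a difference between agents. With no primary scan or contrast named, any of these could later be put forward as the primary result. The statement that 30 volunteers give sufficient power also depends on the family being two.

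**Working it through.** **Inputs from the protocol article**
- Two endpoints, overall level 0.05 two-tailed, SD 10%, power 80% (Sample size): "applying a two-tailed alpha value of 0.05, SD ± 10% and a desired power of 0.80".
- Effects of 8% (grey matter) and 10% (DTI), and 10% for the between-agent difference.
- Three post-anaesthesia scans per session, 30 completers.

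**Step 1: reproduce the plan's figures.** The level is 0.05/2 = 0.025, as stated. The stated sample sizes follow from n = 2(SD/δ)²(z₁₋α/₂ + z₀.₈₀)²:
- 8% at 0.05: 2 × 1.5625 × (1.960 + 0.842)² = 24.5, so 25.
- 10% at 0.05: 2 × 1 × (1.960 + 0.842)² = 15.7, so 16.
- 8% at 0.025: 2 × 1.5625 × (2.241 + 0.842)² = 29.7, so 30.
- 10% at 0.025: 2 × 1 × (2.241 + 0.842)² = 19.0, rounded up to 20.

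All four match. This is the per-group formula for two independent groups. It is used below only because it is the plan's own yardstick.

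**Step 2: count the comparisons that the text supports**
- Two endpoints × (change, between-agent difference) = 4. This needs only the sample-size sections.
- Two endpoints × (change within sevoflurane, change within propofol, difference) = 6. This follows Hypotheses and Outcomes.
- Six × three scans tested separately = 18. This is a worst case.

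**Step 3: family-wise error if each is tested at 0.025.** If the tests were independent, the error would be 1 − 0.975^k. A simulation relaxes independence. It uses 30 volunteers, paired t-tests, no true effect, equal noise at each scan, a shared baseline within each session, and endpoint correlation 0 to 0.5. The 18-test row also varies the correlation between post-anaesthesia scans from 0 to 0.8. The four-test row takes the change as averaged over the two agents.

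| Tests at 0.025 | If independent | Simulated |
|---|---|---|
| 2 | 4.9% | about 5% |
| 4 | 9.6% | 9–10% |
| 6 | 14.1% | 11–12% |
| 18 | 36.6% | 19–29% |

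**Step 4: what a matching correction would cost.** This uses the formula of Step 1, with power at n = 30 equal to Φ(0.8 × √(30/2) − z₁₋α/₂) for the 8% effect.

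| Level | n for 8% effect | Power at n = 30, 8% effect |
|---|---|---|
| 0.05/2 = 0.025 | 30 | 80.4% |
| 0.05/4 = 0.0125 | 35 | 72.6% |
| 0.05/6 = 0.0083 | 38 | 67.7% |

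The 10% effect keeps power of about 92% at 0.05/4 and 89% at 0.05/6, so the cost falls on grey matter.

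**The case against.** Four points can be made for the plan.

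- **A further correction is promised.** Both primary endpoints are MRI data, and Statistical analysis provides Bonferroni or FDR for MRI data. Bonferroni across all primary comparisons would remove the inflation. This stands as far as it goes. But the section leaves the choice between two methods open and does not say which tests form the family, and FDR does not control the family-wise rate. It also does not say which result is primary.
- **0.025 is introduced as a sizing level.** No sentence says that every comparison will be tested at 0.025, and the analysis section itself states 0.05. This is correct, so the error rates above are conditional on that rule. The mismatch between a two-way correction and at least four sized comparisons does not depend on it.
- **Eighteen separate tests is not the stated plan.** A reader might infer that each scan will be tested for each contrast. The documents do not support this: the Outcomes section describes what the design permits, and the summation provision is meant to avoid testing repeated measurements one by one. The 18-test figure is therefore only an upper scenario. The summary is not defined, however, and collapsing the scans still leaves four to six comparisons.
- **The aim is exploratory, and details may sit in an analysis plan.** The Aim does speak of exploring. But the article also states directional hypotheses, primary end points, 80% power and a Bonferroni divisor, and it keeps a separate exploratory tier. The divisor of two and its reuse are stated in this text, so this is not a detail left for later.

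**Conclusion.** The point holds in a limited form. The arithmetic of 0.025 is right, but the family it covers is too small. The sample-size sections alone contain four comparisons under a correction for two, six if change is tested within each agent, and no primary scan or contrast is named.

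If each comparison is tested at 0.025, the false-positive chance is about 9–10% for four and 11–12% for six, against the intended 5%. These figures rest on the simulation assumptions above and on one measure per modality. The 19–29% for 18 tests rests in addition on an assumed between-scan correlation of 0 to 0.8. It should not be read as the plan's expected error rate.

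This should be corrected. The loose correction for MRI data does not repair it, and a change of wording would.

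**What to change.** In Primary outcome and in Correction for multiple comparisons, name for each endpoint one primary contrast at one scan, or one explicitly defined summary over the three scans, and test it at 0.025. Make the remaining contrasts and scans secondary, or test them in a stated fixed order after the primary. State in Statistical analysis that 0.025 applies to these two tests, and say which family the Bonferroni or FDR step covers.

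This needs no extra volunteers or scans, only wording settled before unblinding. The cost is that whatever is not chosen loses primary status, possibly including the change-from-baseline hypothesis or the between-agent hypothesis.

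If all contrasts are to stay primary, state 0.05/4 or 0.05/6 on one named scan or summary and restate the sample size. By the plan's own formula the 8% effect then needs 35 or 38. If 30 is kept, power of about 73% or 68% should be declared in place of 80%.

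### The two primary hypotheses are planned at Bonferroni 0.025 each; Holm's procedure would keep the same 5% familywise control and never have less power, at almost no cost

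*Protocol article*

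**What the plan says.** The Sample size section of the protocol article names two primary end points, grey-matter volume and DTI. The grey-matter calculation is described as "applying a two-tailed alpha value of 0.05, SD ± 10% and a desired power of 0.80"; its result is that "25 subjects will be necessary to detect a difference of 8% in the hippocampal volume between groups". For DTI it says "We assume a 10% change in mean diffusivity", with the same SD, alpha and power, and arrives at 16 volunteers.

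The section Correction for multiple comparisons treats the two end points as dependent and lowers the level: "The desired corrected significance level is 0.025 (significance level of 0.05 Bonferroni corrected for two number of hypothesis". At that level, "this gives a sample size of 30 volunteers regarding detection of statistically significant differences in grey-matter volume"; the DTI requirement becomes 20.

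The section Detection of differences between general anaesthesia methods reuses the level for a 10% difference in both end points: "With a significance level of 0.025 (Bonferroni corrected), SD ± 10% and a power of 80%, the sample size is 20".

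The testing rule is in Statistical analysis. It sets alpha at 0.05 and says "For MRI data, correction for multiple comparisons is performed with" either Bonferroni or the false discovery rate. It does not tie either method to the two primary hypotheses. No step-down rule appears anywhere in the article.

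**The concern.** Bonferroni holds each hypothesis at 0.025 even after the other has been rejected. Holm compares the smaller p-value with 0.025 and, if that is significant, the larger with 0.05. It needs no assumption about how the end points are related, so the dependence that the article mentions is no obstacle.

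On the plan's own figures the correction falls on grey matter. Its requirement goes from 25 to 30, which is the whole sample, while DTI needs 20 and so has power to spare at 30. If both planned effects exist, DTI will usually pass at 0.025, and grey matter could then be tested at 0.05. Staying with Bonferroni gives that up. What is at stake is power on the tighter end point and the chance of succeeding on both. The validity of the trial's conclusions is not at stake.

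**Working it through.** **Inputs.** Effects of 8% (grey matter) and 10% (DTI), SD 10%, power 80%, two-sided alpha 0.05 before correction and 0.025 after, 30 completers. All are from the article. It gives no correlation between the end points; I assume 0 to 0.8.

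**Reproducing the plan's sample sizes.** Normal approximation for two independent means, n per group = 2(z_alpha/2 + z_power)²/d², with d = effect/SD and z_power = 0.8416.

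| Alpha | z_alpha/2 | Grey matter, d = 0.8 | DTI, d = 1.0 |
|---|---|---|---|
| 0.05 | 1.9600 | 2 × 2.8016²/0.64 = 24.53, so 25 | 2 × 2.8016² = 15.70, so 16 |
| 0.025 | 2.2414 | 2 × 3.0830²/0.64 = 29.70, so 30 | 2 × 3.0830² = 19.01, so 20 |

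All four stated figures match. They come from the unpaired, per-group formula, although the volunteers serve as their own controls. Power is therefore shown on both variance bases.

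**Unpaired basis, N = 30.** The test statistics have means 0.8√15 = 3.0984 and 1.0√15 = 3.8730.

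- Grey matter at 0.025: Φ(3.0984 − 2.2414) = 0.8043. At 0.05: Φ(3.0984 − 1.9600) = 0.8725.
- DTI at 0.025: Φ(3.8730 − 2.2414) = 0.9486. At 0.05: Φ(3.8730 − 1.9600) = 0.9721.
- Holm, grey matter, correlation 0: 0.8043 + (0.8725 − 0.8043) × 0.9486 = 0.8690.
- Holm, DTI, correlation 0: 0.9486 + (0.9721 − 0.9486) × 0.8043 = 0.9675.
- Both significant, correlation 0: Bonferroni 0.8043 × 0.9486 = 0.7630; Holm 0.7630 + 0.0682 × 0.9486 + 0.0235 × 0.8043 = 0.8466.

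Integrating the bivariate normal distribution for other correlations:

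| Correlation | Grey matter: Bonferroni → Holm | DTI | Both significant |
|---|---|---|---|
| 0 | 80.4% → 86.9% | 94.9% → 96.7% | 76.3% → 84.7% |
| 0.5 | 80.4% → 86.6% | 94.9% → 96.0% | 78.2% → 85.6% |
| 0.8 | 80.4% → 86.7% | 94.9% → 95.3% | 79.8% → 86.5% |

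A simulation of 2 million draws agrees to within 0.1 point. The chance of at least one significant end point is the same under both methods (99.0% at correlation 0), because Holm's first step is Bonferroni.

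**Paired basis, N = 30** (SD 10% taken as the SD of paired differences). The means become 0.8√30 = 4.3818 and 1.0√30 = 5.4772.

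- Grey matter at 0.025: Φ(4.3818 − 2.2414) = 0.9838. At 0.05: Φ(4.3818 − 1.9600) = 0.9923, which is the most Holm can reach. Holm gives 99.2% at every correlation tried.
- DTI at 0.025: Φ(5.4772 − 2.2414) = 0.9994, so there is almost nothing to gain.

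**If DTI has no effect.** Unpaired, correlation 0: 0.8043 + 0.0682 × 0.025 = 0.8060, a gain of 0.17 points. Over correlations 0 to 0.8 and both variance bases, the gain stays at about 0.2 points or less.

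**Familywise error.** With both effects null, the two methods make a false rejection in exactly the same cases: 1 − 0.975² = 4.94% at correlation 0, and 4.65% at 0.5. With one effect real, Holm never tests the null end point above 0.05, so its error stays at or below 5%.

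**Between-agent comparison** (10% on both end points, unpaired, N = 30). Each end point goes from 94.9% to 97.1% at correlation 0 and to 96.8% at 0.5.

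**The case against.** **No error is shown.** This stands. Bonferroni at 0.025 is valid, its arithmetic is right, and an analysis plan that is not shown could still refine it. The point survives only as an efficiency gain: the article names its correction methods, and one that is never less powerful is available.

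**A reader might infer that the protocol fixes each test at 0.025.** The text does not go that far. The correction section speaks of the level for each sample size estimation, and Statistical analysis leaves Bonferroni or FDR open. Testing at 0.025 is the natural reading, not an explicit rule. The open choice is itself a reason to name one rule, since FDR control does not in general give strong 5% familywise control.

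**A reader might infer a gain of some six points without qualification.** That figure needs both effects to be real and needs the unpaired variance basis. The own-control design suggests that the SD could be that of paired differences, and then the gain is under one point. The article does not say which SD it means.

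**A reader might infer that fewer volunteers would do.** On the unpaired basis Holm passes 80% for grey matter at N = 26 (81.6% at correlation 0, 81.2% at 0.5), but only if DTI delivers. Under Bonferroni the figure at 26 is 74.0%, and with no DTI effect Holm barely improves on it. The documents give no ground for a smaller sample.

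**Two p-values are a simplification.** This also stands. The primary outcome covers volume, morphology and white-matter microstructure, at several time points and for two agents. Holm on two hypotheses presupposes one p-value for each and does not deal with the rest.

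**Conclusion.** A cheap improvement, not an error. For the same two hypotheses and the same 5% familywise level, Holm never has less power than Bonferroni, whatever the dependence.

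At N = 30, with both planned effects real, grey-matter power rises by about 6 points on the unpaired basis (80.4% to 86.6–86.9%) and by about 0.8 points on the paired basis (98.4% to 99.2%). The chance of both end points being significant rises by about 7 to 8 points on the unpaired basis. With no DTI effect the grey-matter gain is about 0.2 points or less.

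These sizes rest on the article's effects and SD, on normally distributed test statistics, and on an assumed correlation of 0 to 0.8. That Holm is never worse rests on none of them.

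**What to change.** In Statistical analysis and in Correction for multiple comparisons, state that the two primary p-values (grey-matter volume and DTI) are compared by Holm's procedure at familywise alpha 0.05: the smaller against 0.025 and, if it is significant, the larger against 0.05. Let this replace the choice of Bonferroni or FDR for these two hypotheses. Apply the same rule in Detection of differences between general anaesthesia methods.

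Keep N = 30, and keep the 0.025 calculation as a conservative planning bound that does not depend on the other end point succeeding.

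The cost is a sentence or so in each section, with no extra volunteers or procedures. There is one small downside. If 97.5% intervals are reported, an end point declared significant at Holm's second step can have an interval that includes zero, and the report should say so. Multiplicity across regions, time points and agents needs its own rule, which this change does not supply.
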